#### Interventions in the Cardio-Metabolic clinic:

Participants in the CMC will follow a decision-making treatment algorithm in the REDCap-system. The treatment algorithm is coded in accordance to the most recent guidelines and recommendations for diabetes management and CVD (32). Consequently, there may be modifications over time. Participants will be categorized into various cardiovascular risk groups using the SCORE2-Diabetes (Figure 2) (32) and will receive interventions targeting nine specific areas (Figure 3); dyslipidemia, hypertension, thrombosis prophylaxis, diabetes management, assessment of microvascular complications, evaluation of SGLT2i and/or GLP1-RA, lifestyle modifications, peripheral artery disease, and vaccinations. The CMC intervention is considered complete when a participant is fully titrated to the targeted or highest tolerated dose in all suggested treatment areas. Endpoint assessments will begin once intervention is completed.

[figure not shown]

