## Treatment algorithm:

**Figure 3. Overview of the treatment algorithm in the CMC**

**
[figure not shown]
**

- Dyslipidemia:
  Dyslipidemia is assessed by LDL status in blood samples. Patients are classified according to table 1 (32). Patients with moderate CV risk; will be recommended a LDL <2.6 mmol/L.
  Patients with high CV risk; will be recommended a LDL <1.8 mmol/L.
  Patients with very high CV risk; will be recommended a LDL <1.4 mmol/L (32).

If LDL exceed these thresholds, the treatment algorithm will be according to the following order: 1) High dose Atorvastatin, 2) Ezetimibe, 3) Referral to lipid-clinic.

- Hypertension:
  Blood pressure is measured in the examination, patients with a blood pressure >130/80 mmHg are instructed in measurement of blood pressure at home 3 times a day for three days (32). If the mean home blood pressure is >130/80 mmHg, treatment algorithm will be according to the following order:

1) ACE-inhibitor or angiotensin II receptor blocker (ARB), 2) thiazide, 3) calcium antagonist, 4) mineralocorticoid (MRA), and 5) beta blocker. If aforementioned is already supplied 6) Referral to hypertension-clinic.

In patients with a high biological age blood pressure <140/85 mmHg is accepted. Blood pressure >140/85 mmHg the above-mentioned treatment algorithm will be followed (32).

- Thrombosis prophylaxis:
  Patients with ischemic heart disease are recommended lifelong acetylsalicylic acid.
  If patients have had a new acute myocardium infarction, they will be prescribed 12 months of ADP-receptor blocker (32).

Patients with cerebrovascular disease are recommended lifelong clopidogrel treatment(32) . Patients with periphery arterial disease are recommended lifelong ASA treatment (32).

Patients with atrial fibrillation/flutter are recommended lifelong direct oral anti-coagulant (DOAC) treatment (32).

When two antithrombotic drugs are used, proton pump inhibitors are recommended to prevent gastrointestinal bleeding(32).

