### Peripheral artery disease/foot ulcer:

1) Patients with critical ischemia (including: resting pain, ischemic ulcers, or gangrenous ulcers) will be referred to the outpatient clinic of vascular surgery (32, 37).

2) Patients with or without symptoms of intermittent claudicatio and ABI>1,4 will be referred to examination with toe-brachial index (TBI) at the department of Endocrinology. If TBI is abnormal, patients will be diagnosed with lower extremity artery disease (LEAD), and treatment with ASA and high dose statins therapy will be initiated. Target LDL level <1.4 mmol/L (32, 37).

3) Patients with or without symptoms of intermittent claudicatio and ABI<0.9 are diagnosed with lower extremity artery disease (LEAD), and treatment with ASA and high dose statins therapy will be initiated. Target LDL level <1.4 mmol/L (32, 37).

4) Patients with diabetic foot ulcers will be referred to the outpatient clinic for wounds (32, 37).

5) Patients with abnormal monofilament test and symptoms of neuropathy will be referred to the department of endocrinology (32).

- Vaccinations:
  Anamnesis regarding vaccination status is obtained, and recommendations of yearly influenza vaccination (38). COVID vaccinations (39) after current local guidelines.

Examinations
1) Blood samples will be drawn at the baseline visit and at the three years follow-up visit. Approximately 80 ml of blood will be collected. Blood samples will be analyzed for; Hematology: Hemoglobin and leucocytes.
Lipid profiles: Total cholesterol, high-density lipoprotein (HDL), low-density lipoprotein (LDL), and triglycerides. Diabetes status: Glycated haemoglobin (HbA1c). Liver function: Alanine transaminase (ALAT), alkaline phosphatase, and gamma-glutamyl transferase (GGT), lactate dehydrogenase (LDH), and FIB-4 index for liver fibrosis assessment. Cardiac markers: N-terminal-pro b-type natriuretic peptide (NT-proBNP) and troponin T. Electrolytes: Sodium and potassium. Renal function: Creatinine and estimated glomerular filtration rate. Inflammatory marker: C-reactive protein (CRP).

2) Urine samples will be collected at the baseline visit and at the 3 year follow-up visit and albuminuria will be evaluated. This will include measurement of urine albumin and creatinine to calculate the albumin creatinine ratio (UACR) from a spot urine sample.

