**Figure 4 - Timeline for the study**

[figure not shown]

Outcomes The primary outcome is the time to the first occurrence of a composite of CV deaths, non-fatal myocardial infarction, non-fatal stroke, and hospitalization for heart failure.

The secondary outcomes are the time to the first occurrence of one of the single components of the primary outcome, and a combination of the single components of the primary outcome to assess the total symptom burden. Additional secondary outcomes will be the assessment of microvascular complications, protocol driven medical changes and a cost-effectiveness analysis of the Cardio Metabolic Clinic. Primary and secondary outcomes and endpoints are shown in the following table:

| **Primary outcomes** | **Primary endpoints** |
| --- | --- |
| To examine whether patients with type 2 Diabetes (T2D) receiving optimal diabetes care in a Cardio-Metabolic Clinic are superior compared to usual care in reducing; incidence of cardiovascular (CV) death, non-fatal acute myocardial infarction (AMI), non-fatal stroke, and hospitalization for heart failure (HF) | Time to the first occurrence of major adverse cardiovascular event (MACE), a composite endpoint consisting of:   - CV death - Non-fatal AMI - Non-fatal stroke - Hospitalization for HF |
| Units of measure: Measured in days. | Time frame: From baseline to 5 years of follow-up (FU). |

| **Secondary outcomes** | **Secondary endpoints** |
| --- | --- |
| To examine whether patients with type 2 Diabetes (T2D) receiving optimal diabetes care in a Cardio-Metabolic Clinic are superior compared to usual care in reducing; incidence of cardiovascular (CV) death, non-fatal acute myocardial infarction (AMI), non-fatal stroke, and hospitalization for heart failure (HF) | Time to the first occurrence of MACE, a composite endpoint consisting of:   - CV death - Non-fatal AMI - Non-fatal stroke - Hospitalization for HF |
| Units of measure: Measured in days. | Time frame: From baseline to 10 years FU. |
| To compare the individual component, CV death, of the primary endpoint in patients receiving optimal diabetes care in a Cardio-Metabolic Clinic versus usual care. | Time to the first occurrence of:   - CV death   (Presumed cardiac condition leading to death. Including: AMI, venous thromboembolic event, malignant arrhythmia, cardiogenic shock, fatal stroke and aorta dissection) |
| Units of measure: Measured in days. | Time frame: From baseline to 5 + 10 years of FU. |

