| To compare the occurrence of macrovascular complications, peripheral artery disease (PAD) and/or ischemic heart disease (IHD), in patients receiving optimal diabetes care in a Cardio-Metabolic Clinic versus usual care | Time to first occurrence of a composite macrovasucular endpoint comprising:   - new diagnosis of lower extremity arterial disease (LEAD), - new/progression of foot ulcers, - surgical procedures related to PAD - coronary revascularization   Surgical procedures includes: percutaneous transluminal angioplasty, peripheral artery bypass, thrombectomy, thrombolysis, amputations.  Coronary revascularization includes: percutaneous coronary intervention (PCI), coronary artery bypass graft. |
| Units of measure: Measured in count of events. | Time Frame: From baseline to 3 years of FU. |
| To compare the occurrence of macrovascular complications in the lower extremities, in patients receiving optimal diabetes care in a Cardio-Metabolic Clinic versus usual care | - Change in ankle-brachial pressure index (ABI) |
| Units of measure: Measured in ratio to baseline. | Time Frame: From baseline to 3 years of FU. |
| To compare change in protocol-driven medication in patients receiving optimal diabetes care in a Cardio-Metabolic Clinic versus usual care | Change in protocol-driven medication:   - Lipid lowering medication - Antihypertensive medication - Anti-thrombotic medication - Anti-diabetic medication - Nephro-protective medication |
| Units of measure: Measured in percentage [%]. | Time Frame: From baseline to 3 years of FU. |
| To compare change in patient experienced symptoms in patients receiving optimal diabetes care in a Cardio-Metabolic Clinic versus usual care | - Change in symptoms as reported by patients using the Kansas City Cardiomyopathy Questionnaire (KCCQ) |
| Units of measure: Measured in score points (change in percentage [%]). | Time Frame: From baseline to 3 years of FU. |
| To compare the net cost of implementing a Cardio-Metabolic Clinic in patients receiving optimal diabetes care versus usual care | - Net cost of a Cardio-Metabolic Clinic:  Cost of Cardio-Metabolic Clinic minus averted costs   Averted costs includes: averted admissions, medical treatment, and productivity). |
| Units of measure: Measured in dollars [$]. | Time frame: From baseline to 5 + 10 years of FU. |

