# Ethics and dissemination

**Ethics**

The study complied with the Declaration of Helsinki, and was approved by the local ethics committee (Project-ID: S-20230015). When participating in this study, the intervention will consist of an intensive effort in diabetes care based on the most recent guidelines and recommendations. Whereas, the control group will receive the standard of care from their regular physician(s). Therefore, in theory, the treatment should be the same, and we do not anticipate any associated risks. However, we anticipate that a comprehensive evaluation and examination will lead to significant differences in the treatment regimen. Considering this, we expect a therapeutic gain, both in CVD death and diabetic microvascular complications for the participants receiving the intervention. The participants in the control group will receive the standard of care, thus, there are no ethical considerations.
The local ethical committee will be notified of a protocol amendment if any changes to the research project could potentially affect the participants.

The national patient insurance will cover the participants. No compensation or remuneration will be provided for participation in the study.

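### The protocol anticipates no risk while expecting treatment to differ between arms, and no listed outcome shows bleeding separately although antithrombotic treatment is part of the intervention

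*Protocol*

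**What the plan says.** **Risk statement (Protocol, Ethics and dissemination, Ethics).** The reasoning begins "in theory, the treatment should be the same, and we do not anticipate any associated risks. However, we anticipate that a comprehensive evaluation" and continues that this "will lead to significant differences in the treatment regimen. Considering this, we expect a therapeutic gain". The gain is located in cardiovascular death and microvascular complications. No harm is named.

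**Intervention (Protocol, Interventions in the Cardio-Metabolic clinic; Treatment algorithm).** The nine target areas include "thrombosis prophylaxis, diabetes management, assessment of microvascular complications". Antithrombotic treatment follows diagnosis. "Patients with ischemic heart disease are recommended lifelong acetylsalicylic acid"; clopidogrel is advised after cerebrovascular disease, ASA in peripheral arterial disease, an ADP-receptor blocker for 12 months after a new infarction, and a DOAC in atrial fibrillation or flutter. The section on peripheral artery disease adds: "Patients with or without symptoms of intermittent claudicatio and ABI<0.9 are diagnosed with lower extremity artery disease (LEAD), and treatment with ASA". The protocol recognises the corresponding harm once: "When two antithrombotic drugs are used, proton pump inhibitors are recommended to prevent gastrointestinal bleeding".

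**Outcomes (Protocol, Outcomes tables).** The medication-change endpoint includes "Anti-thrombotic medication - Anti-diabetic medication - Nephro-protective medication". No row names bleeding. The primary composite counts non-fatal stroke without giving a subtype. The separate non-fatal stroke row mentions thromboembolic and undetermined types only. The definition of cardiovascular death includes fatal stroke, again without subtype.

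**Event capture (Protocol, Five year follow-up; Ten year follow-up).** Events for the primary and secondary endpoints are taken from a journal audit and a Danish Health Data Authority look-up.

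**The concern.** The absence of risk is argued from equality of treatment, and the next sentence gives that equality up. The trial's hypothesis also needs treatment to differ. If regimens differ enough to lower cardiovascular death, they may also differ enough to change harms.

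Bleeding is the clearest case. The algorithm can add antithrombotic drugs, including in symptom-free patients whose low ankle-brachial index is found at screening. The index is measured in everyone at baseline, but the algorithm is activated only in the clinic arm.

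Followed as written, the trial could report more antithrombotic use and fewer MACE in the clinic arm with no bleeding comparison beside them. A reader deciding whether to adopt the clinic would see the intended benefit of these drugs but not their main cost.

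**Working it through.** The core of the point is textual, and the protocol gives no figure to reproduce.

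**Step 1: the risk statement.** Premise: treatment should be the same in both arms. Conclusion: no risk. Next sentence: treatment is expected to differ markedly. The premise no longer supports the conclusion, and no other ground is offered.

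**Step 2: the outcome list.** Each endpoint in the primary and secondary tables was checked for whether it would show bleeding.

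| Group | Endpoints | Shows bleeding separately? |
| --- | --- | --- |
| MACE to 5 years (primary) and 10 years | 2 | No; haemorrhagic stroke may count, undistinguished |
| CV death, infarction, stroke, heart failure | 4 | No; fatal stroke has no subtype |
| Total count of MACE components | 1 | No |
| Retinopathy | 1 | No |
| eGFR, UACR, CKD stage, CKD composite | 4 | No |
| FIB-4, Fibro-scan | 2 | No |
| Macrovascular composite, ankle-brachial index | 2 | No |
| Medication change | 1 | No; shows exposure only |
| KCCQ | 1 | No |
| Net cost, QALY, cost-effectiveness ratio | 3 | No; may reflect bleeding indirectly |

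Total: 2 + 4 + 1 + 1 + 4 + 2 + 2 + 1 + 1 + 3 = 21 endpoints, of which 0 isolate bleeding. Haemoglobin is drawn at baseline and 3 years (Examinations), but it is a laboratory value and not a listed clinical outcome.

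**Step 3: what an added outcome could deliver.** The protocol gives no bleeding rate. *Assumption:* a 5-year risk of hospitalisation for bleeding of 3% to 10%. Arm sizes: 1500 at 2:1 gives 1000 and 500; the 1306 of the sample size section gives about 871 and 435.

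The half-width of the 95% confidence interval for the risk difference, with the same risk p in both arms, is 1.96 × √[p(1−p)(1/n₁ + 1/n₀)].

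- p = 3%: 1.96 × √(0.0291 × 0.003) = 1.8 points
- p = 10%: 1.96 × √(0.09 × 0.003) = 3.2 points

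The smallest excess d in the clinic arm found with 80% power (two-sided 5%) solves d = (1.96 + 0.84) × √[(p+d)(1−p−d)/n₁ + p(1−p)/n₀], where p is the control risk.

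| n (clinic/control) | Risk | Expected patients at equal risk | Half-width (points) | Detectable excess (points) |
| --- | --- | --- | --- | --- |
| 1000/500 | 3% | 30/15 | 1.8 | 3.0 |
| 1000/500 | 5% | 50/25 | 2.3 | 3.7 |
| 1000/500 | 10% | 100/50 | 3.2 | 4.9 |
| 871/435 | 3% | 26/13 | 2.0 | 3.2 |
| 871/435 | 5% | 44/22 | 2.5 | 4.0 |
| 871/435 | 10% | 87/44 | 3.5 | 5.3 |

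With 1500 participants, the detectable excess is a doubling at a control risk of 3% (3% to 6%) and about half again at 10% (10% to 14.9%).

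**The case against.** The strongest reply has four parts.

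- **The Ethics wording is a concession.** Both arms are entitled to guideline care, no experimental product is given, and the risks meant may be those beyond guideline care. That is a possible reading. The text is still one-sided, because it derives gain from the expected difference and derives nothing else. Rewording the sentence would, however, change no result by itself.
- **Safety tabulation can sit in a statistical analysis plan.** Such a plan may exist, and nothing in the protocol bars counting bleeds. This stands. But the protocol fixes the endpoint list, ties the event reviews to it, and by asserting no risk gives analysts no reason to look further.
- **Harm is not wholly invisible.** Haemorrhagic stroke can count against the clinic in MACE, fatal stroke counts in cardiovascular death, and QALYs would fall with lasting harm. Mitigation is also written in: stomach protection with two antithrombotics, cardiologist review, monitoring visits, and discontinuation for safety. All of this stands, but none of it yields a bleeding comparison.
- **The estimate would be imprecise.** If, say, 20% of clinic patients had antithrombotics added (an assumption), an arm-wide excess of 3.0 to 4.9 points would require about 15 to 25 points among them (3.0/0.20 to 4.9/0.20). This limits what the addition can show and is a reason to keep it descriptive.

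A reader might infer that the clinic arm will bleed more. The documents do not show this: controls may receive the same drugs, and some patients enter already on ASA. A reader might also infer that haemorrhagic stroke is excluded from the primary outcome. The composite gives no subtype, and the stroke row is not worded as an exclusion. Nor can it be inferred that participants are not told of bleeding, since the participant information is not at hand.

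**Conclusion.** The point holds in limited form. The protocol's ground for anticipating no risk is contradicted by its next sentence, and 0 of 21 listed endpoints show bleeding separately, although antithrombotic treatment is one of the intervention areas and its change is itself an outcome. The primary analysis, its test and the sample size are unaffected. What is affected is the safety conclusion, which would lack a between-arm bleeding result. Whether bleeding differs between arms is unknown.

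The precision figures rest on the assumed 3% to 10% risk. They size a possible addition and are not evidence of an error in the plan. This is a cheap improvement worth making.

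**What to change.** Add one descriptive safety outcome: hospitalisation for bleeding or fatal bleeding, including haemorrhagic stroke, in both arms at 5 and 10 years. Including fatal bleeding captures deaths without an admission. Take it from the journal audit and Danish Health Data Authority look-up already planned, and report it by arm with a confidence interval beside MACE, outside the testing hierarchy. Fix the definition before the 5-year review, which the Timeline places at about January 2031.

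As an accompanying edit, replace the no-risk sentence in the Ethics section with one that names bleeding as a possible consequence of intensified antithrombotic treatment.

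Cost: one extra code set, one extra descriptive analysis and one sentence, with no extra visits. The price in interpretation is an imprecise estimate, so a finding of no clear difference must not be reported as evidence of no excess.

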**Data protection and access**

The law regarding General Data Protection Regulation and the Data Protection Act will be followed in the management of personal information (i.e. journal or health information). All information will be stored according to the National Danish Data Protection Agency and only persons with secrecy and connection to the study will access the data. Permission to process and store data was granted by the regional data protection agency at Odense University Hospital, and participant data will be stored using this electronic case-report form in REDCap.

**Dissemination policy**

We will make efforts to publish all the results from this study in international peer-reviewed journals. Study information will be disclosed at ClinicalTrials.gov, and regardless of whether the outcomes are positive, negative, or inconclusive, they will be published on the website (www.clinicaltrial.gov). Participant data will be analyzed as groups, ensuring their confidentiality and preventing identification by others. Authorship of publications will be in accordance with the Vancouver style by the International Committee of Medical Journal Editors.

Financing The Cardiovascular Research Unit has taken the initiative for this research project.
External funding of 1.260.000 kr was received from ”Ramme for højt specialiseret funktion og strategiske indsatsområder” from OUH/Region South Denmark.
 Applications for further financing will be applied.

